# Impact of Chronic Use of Antimalarials on SARS-CoV-2 Infection in Patients With Immune-Mediated Rheumatic Diseases: Protocol for a Multicentric Observational Cohort Study

**DOI:** 10.2196/23532

**Published:** 2020-10-14

**Keywords:** COVID-19, SARS-CoV-2, coronavirus, antimalarial, rheumatic diseases, mortality, immune system, immunology, protocol, observational, pharmacological, drug

## Abstract

**Background:**

COVID-19, caused by the virus SARS-CoV-2, has brought extensive challenges to the scientific community in recent months. Several studies have been undertaken in an attempt to minimize the impact of the disease worldwide. Although new knowledge has been quickly disseminated, including viral mechanisms, pathophysiology, and clinical findings, there is a lack of information on the effective pharmacological management of this disease. In vitro studies have shown some benefits related to the use of antimalarials (chloroquine and hydroxychloroquine) for inhibiting SARS-CoV-2. However, the data from open clinical trials on COVID-19 patients are controversial.

**Objective:**

We present the protocol for a research project that compares the potential protective effect of antimalarials in preventing moderate-to-severe forms of COVID-19 in two groups: (1) patients treated chronically with antimalarials for rheumatic diseases and (2) other members of the patients’ household who have not been diagnosed with rheumatic diseases and are not taking antimalarials.

**Methods:**

This is a 24-week, prospective, observational cohort study comprising patients from public and private health services across Brazil, who chronically use antimalarials for the treatment of immune-mediated rheumatic diseases, osteoarthritis, or chikungunya-related arthropathy. A total of six sequential phone interviews were scheduled during the COVID-19 outbreak in five different regions of Brazil. Information regarding social, epidemiological, and demographic data, as well as details about rheumatic diseases, antimalarials, comorbidities, and concomitant medication, is being recorded using a specific online form in the REDCap database. Symptoms suggestive of COVID-19, including fever, cough, dyspnea, anosmia, and dysgeusia, are being self-reported and collected via phone interviews. Our main outcomes are hospitalization, need of intensive care unit, and death.

**Results:**

Recruitment began at the end of March 2020, and the inclusion was done during an 8-week period (from March 29 to May 17) with a total of 10,443 individuals enrolled at baseline, 5166 of whom have rheumatic diseases, from 23 tertiary rheumatology centers across 97 Brazilian cities. Data analysis is scheduled to begin after all inclusion data have been collected.

**Conclusions:**

This study, which includes a large sample of chronic antimalarial users, will allow us to explore whether SARS-CoV-2 infection may be associated with immune-mediated rheumatic diseases and long-term antimalarial usage.

**Trial Registration:**

Brazilian Registry of Clinical Trials RBR–9KTWX6; http://www.ensaiosclinicos.gov.br/rg/RBR-9ktwx6/

**International Registered Report Identifier (IRRID):**

DERR1-10.2196/23532

## Introduction

COVID-19, which originated from Wuhan, China, in December 2019, remains a major challenge for scientists and the medical community as it continues to spread rapidly across the world [1,2]. The rapid transmission of the disease, which is caused by the novel coronavirus SARS-CoV-2, and the need to minimize its impact have caused scientific research and information to emerge at a record speed, but there are still numerous knowledge gaps [3-6].

In recent months, a marked information revolution has been observed, relating to viral mechanisms, pathophysiology, and heterogeneous clinical findings with different severity grades. Those infected with COVID-19 range from asymptomatic individuals to critically ill patients with outcomes like severe acute respiratory syndrome, coagulopathy (a prothrombotic state triggered by inflammation and other factors), and death [7-13]. Age and concomitant diseases, especially hypertension, diabetes, and heart, kidney, and lung diseases, are associated with poor outcomes [14-18].

Considering there is no specific, effective pharmacological treatment for COVID-19, several drugs have been tested, such as antivirals (lopinavir-ritonavir, remdesivir, favipiravir); antimalarials alone or combined with azithromycine; interleukin 6 (IL-6) antagonists; Janus kinase inhibitors and interferon, as well as other procedures (extracorporeal membrane oxygenation and convalescent plasma). However, to date, there are no data on the potential preventive effect of any of these, regardless of timing (pre-exposure, symptomatic period, or inflammatory phase) [19-27].

The role of chloroquine and hydroxychloroquine in treating patients with malaria and immune-mediated rheumatic diseases (IMRD) is well-known, especially in cases of systemic lupus erythematous and rheumatoid arthritis. In vitro studies have shown antimalarials have an antiviral effect against some viruses, such as SARS-CoV (severe acute respiratory syndrome–associated coronavirus), MERS-CoV (Middle East respiratory syndrome coronavirus), SARS-CoV-2, HIV, Zika, and influenza A(H5N1), especially in relation to endosomal membrane pH changes and an inhibitory mechanism to hamper the viral entry inside the cells. However, clinical trials are controversial and present many methodological problems, including randomization, dosage, time of use, endpoint definitions, outcomes, and safety issues [28-35].

Among rheumatologists, antimalarials have been used safely and effectively for several decades in patients with rheumatic diseases [36]. For this reason, rheumatologists and rheumatic patients who are long-term users of antimalarials were involved in COVID-19–related discussions and research [37-39]. Our main hypothesis is that patients with rheumatic diseases who chronically use antimalarials could have a lower rate of moderate-to-severe forms of COVID-19 since these drugs work as immune modulators in mitigating cytokine storm and poor prognosis.

### Objectives

Our primary aim is to assess the potential preventive effects of antimalarials in reducing the incidence of moderate-to-severe forms of COVID-19 in patients with rheumatic diseases. Secondarily, we aim to determine the frequency of SARS-CoV-2 infection in patients with rheumatic diseases who are chronic users of antimalarials. For both objectives, patients with rheumatic diseases will be compared with members of their household who are not taking antimalarials.

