**Figure 3 figure3:**
[figure not shown]
Suspected vs confirmed cases of COVID-19. RT-PCR: real-time polymerase chain reaction, IgM: immunoglobulin M, IgA: immunoglobulin A, IgG: immunoglobulin G, ELISA: enzyme-linked immunosorbent assay, IC: ion channel, ECLIA: electrochemiluminescence immunoassay.

Moderate-to-severe cases are defined as those that require hospitalization, mechanical ventilation, or result in death. Through direct contact with hospitals, hospitalized patients are being clinically evaluated in terms of longitudinal follow-up and treatment outcome, infection severity, length of stay, need for intensive care, mechanical ventilation, and cause of death.

Considering the heterogeneous community viral transmission in Brazil, some epidemiological approaches were developed to assure a similar path involving patients with rheumatic diseases and controls, such as the same pandemic COVID-19 curve in each city and region [41]. Therefore, after initial contact (V1), two strategies were adopted to maintain the follow-up of patients and to optimize the capture of main outcomes. Firstly, an active strategy is addressed in cases of flu-like syndrome and symptoms suggestive of COVID-19. For this strategy, the patient or household member is shown how to provide clinical data on the patient or his/her control through a toll-free telephone number (the 0800 system). Secondly, the patient is contacted every week by the REDCap team to gather relevant data on infection. An additional visit is conducted if the patient or control provides information about flu symptoms or disease activity via an unscheduled phone call or contact through the toll-free number. In both cases the individual will be advised to stay home and use painkillers or an antipyretic. In case of worsening/severe symptoms (eg, persistent cough or fever and shortness of breath), they will be advised to visit a hospital or to make an appointment with a physician involved in our study.

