## Discussion

This study’s novel design, with its large sample of chronic antimalarial users, will enable us to perform a thorough prospective assessment (every 2 weeks) to explore whether vulnerability to SARS-CoV-2 infection may be associated with IMRD or to hydroxychloroquine after adjustments for cofounders, especially those related to other immunosuppressive drugs and comorbidities. On the other hand, it has some limitations, such as compliance and adherence; a potential shortage of HCQ (hydroxychloroquine) in some parts of our country; possible biases associated with recalling symptoms; inability to answer the phone (due to hospitalization or death), and lack of confirmatory tests (PCR tests for SARS-CoV-2 or antibody-based RNA [ribonucleic acid]) for all enrolled patients and controls, especially in those with nonsevere forms. Future randomized controlled trials may provide a better understanding of these differences.

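### The infection aim and conclusions are answered by counts of reported, suspected or confirmed illness, so a lower rate in antimalarial users could not be read as fewer SARS-CoV-2 infections

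*Protocol article*

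**What the plan says.** The Objectives section of the protocol article gives the secondary aim: "we aim to determine the frequency of SARS-CoV-2 infection in patients with rheumatic diseases who are chronic users of antimalarials", with household members not taking antimalarials as the comparison. The abstract's Conclusions say the study will "explore whether SARS-CoV-2 infection may be associated with immune-mediated rheumatic diseases and long-term antimalarial usage", and the Discussion speaks of vulnerability to infection in the same sense.

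The Introduction recognises silent infection: "Those infected with COVID-19 range from asymptomatic individuals to critically ill patients". It also gives the reason for expecting a benefit: "these drugs work as immune modulators in mitigating cytokine storm and poor prognosis".

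On measurement, the abstract's Methods say that symptoms "are being self-reported and collected via phone interviews". In the follow-up text of the Data Collection section, "an active strategy is addressed in cases of flu-like syndrome and symptoms suggestive of COVID-19", and "the patient is contacted every week by the REDCap team to gather relevant data on infection". The case definition in the same section rests on a symptom list and/or contact with a case, with PCR or serology for confirmation. The Outcomes section lists infection, glossed as illness, and pools suspected, suggestive and confirmed cases. The Statistical Analysis section dates the event at confirmed or merely suspected illness. No testing irrespective of symptoms is described. The Discussion concedes that confirmatory tests are lacking "for all enrolled patients and controls, especially in those with nonsevere forms".

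**The concern.** The aim names one quantity and the plan measures another. If the same share of infections were missed in both groups, the ratio between groups would stay roughly right. Here the share missed may depend on exposure. Being counted depends on having symptoms, being confirmed depends on severity, and the drugs are hypothesised to make the illness less severe. A contrast labelled infection may therefore mix an effect on acquiring the virus with an effect on showing symptoms or being tested. The Discussion admits that tests are missing but does not draw this consequence, and the infection wording stays.

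The same mechanism distorts any severity comparison made only among detected or confirmed cases, because the exposure may change who enters that set.

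**Working it through.** The plan gives no expected infection frequency, so it has no figure of its own to reproduce on this point. The Sample Size section concerns the moderate-to-severe rate.

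**From the article.** 10,443 enrolled, 5166 with rheumatic disease, so 10,443 − 5166 = 5277 controls. Significance at P<.05.

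**Assumed, not in the article.** True infection risk 10% in both groups (true ratio 1.00); 40% of infections asymptomatic; 20% of symptomatic cases moderate-to-severe; no clustering. Per infection, the mild symptomatic share is 0.60 × 0.80 = 0.48 and the severe share 0.60 × 0.20 = 0.12. Rejection probabilities are for a two-sided two-proportion z-test.

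**Case A: the drug silences 25% of mild cases and does nothing else.**
- Ratio = [0.48 × (1 − 0.25) + 0.12] / (0.48 + 0.12) = 0.48 / 0.60 = 0.80.
- Reported rates are 4.8% in users and 6.0% in controls. P<.05 occurs in about 77% of studies.
- Over true infection 5% to 15% and asymptomatic share 20% to 40%, the range is 47% to 98%.
- If only 10% of mild cases are silenced, the ratio is (0.48 × 0.90 + 0.12) / 0.60 = 0.92 and the rejection probability about 18%.

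**Case A with false positives.** With a false-positive rate f among the uninfected, the rates become 0.048 + 0.90f and 0.060 + 0.90f.

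| f | Users | Controls | Ratio | P<.05 |
|---|---|---|---|---|
| 0% | 4.8% | 6.0% | 0.80 | 77% |
| 2% | 6.6% | 7.8% | 0.85 | 66% |
| 5% | 9.3% | 10.5% | 0.89 | 54% |
| 10% | 13.8% | 15.0% | 0.92 | 42% |
| 15% | 18.3% | 19.5% | 0.94 | 35% |

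**Case B: the drug moves 25% of severe cases to mild.** This is closer to the hypothesis in the Introduction. Users have 0.12 × 0.75 = 0.09 severe and 0.48 + 0.03 = 0.51 mild.
- Symptom-based count: 0.51 + 0.09 = 0.60 in users and 0.60 in controls. Ratio 1.00, no artefact.
- Confirmed cases only, assuming 20% of mild and 90% of severe cases are tested: users 0.51 × 0.2 + 0.09 × 0.9 = 0.183; controls 0.48 × 0.2 + 0.12 × 0.9 = 0.204. Ratio 0.183 / 0.204 = 0.90. At 10% infection the rates are 1.83% and 2.04%, and P<.05 occurs in about 12% of studies.
- With mild testing of 10% to 50% the ratio runs from 0.85 to 0.97. With infection of 5% to 15% as well, rejection runs from about 6% to 24%.

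**Severity among detected cases.** In Case A the severe share is 0.12 / 0.48 = 25% in users and 0.12 / 0.60 = 20% in controls: users look worse although no severe case was added. In Case B the true ratio of severe cases per person enrolled is 0.09 / 0.12 = 0.75. Among confirmed cases the severe shares are 0.081 / 0.183 = 0.443 and 0.108 / 0.204 = 0.529, a ratio of 0.84, so the benefit looks smaller than it is.

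**The case against.** A reader might infer that the study cannot see mild infection at all and would report mere softening of symptoms as prevention of infection. The article does not support either step.

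- Mild illness is counted. The symptom list includes nasal congestion, malaise and cough, suspected cases are outcomes, and there are weekly calls and a toll-free line. What is often missing in mild cases is laboratory confirmation. The contact criterion can even classify a person without symptoms, although contact does not show infection.
- The stated hypothesis is about severe disease. A shift from severe to mild leaves the symptom-based count unchanged. The larger artefact needs mild cases to become silent, which the article does not hypothesise.
- The language is cautious. Preventive effects are claimed only for moderate-to-severe disease; infection is a matter of frequency and possible association. The outcome is glossed as illness, and the Discussion discloses missing tests and recall bias and points to randomised trials.
- False positives dilute the artefact, and the net direction is not fixed. Rheumatic symptoms could raise the count in patients, and giving priority to a symptomatic first control could raise it in controls.
- The primary aim already concerns the incidence of moderate-to-severe disease, and nothing says severity tests will be confined to detected cases. The figures and the data form are not shown, so details of the case definition cannot be checked.

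All of this limits the size and certainty of the error. It does not close the gap between the aim and the measurement. Disclosing that tests are missing does not tell the reader that the between-group contrast may then reflect symptom expression, and uncertainty about direction is a further reason not to call the count infection frequency.

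**Conclusion.** The point stands as a mismatch between the named aim and the measured outcome. Asymptomatic infection is not systematically detected, mild illness is counted but often unconfirmed, and the infection contrast could fall below 1 with no infection prevented if exposure makes cases silent or too mild to report or test.

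That it will do so is not shown. The size runs from no artefact at all (severe-to-mild shift, symptom-based count), through a ratio of about 0.90 with about 12% rejection (same shift, confirmed cases), to a ratio of 0.80 with about 77% rejection (25% of mild cases silenced, no false positives), the last falling to between 66% and 35% with 2% to 15% false positives. Every epidemiological input is an assumption; only the group sizes and the significance level come from the article. The mismatch affects the secondary aim and the first listed outcome. The hospitalisation, intensive care, ventilation and death outcomes are not affected in this way.

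**What to change.** Restate three places as reported suspected or symptomatic COVID-19 illness: the secondary aim in Objectives, the first item in Outcomes, and the conclusions in the abstract and the Discussion. Report laboratory-confirmed COVID-19 separately. State that a lower rate in antimalarial users will not be read as fewer infections.

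For the secondary severity comparisons in Outcomes, base between-group inference on moderate-to-severe COVID-19 per person enrolled, which the primary aim already implies, and treat severity among detected or confirmed cases as descriptive.

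This needs only changes of wording and a stated denominator. No new data are required, and the article says analysis has not started. The downside is a narrower claim: the study would no longer speak to infection as such.

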## Methods

### Design

The study design will be a prospective, multicentric, observational cohort study with a control group.

### Sample Size

Considering a moderate-to-severe COVID-19 rate as the dependent variable, a rate which the current literature estimates to be 20% [4,6,10-18,40-42] as well as the proportion of 1 case for every 2 controls, the sample calculation was approximately 3000 antimalarial users and 6000 nonusers, with an error α=5% and β=20%.

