### Control Group

The control group will consist of healthy individuals aged >18 years, who are household cohabitants or work colleagues of patients with rheumatic diseases in the intervention group.

Contact with a suspected or confirmed case of COVID-19 is defined as an individual sharing accommodations with a patient with a rheumatic disease (eg, residing in the same house or environment as roommates, occupational colleagues, etc). The exposure grade assessment is individualized, considering the type of environment and the exposure time.

For each case, two household and/or professional contact individuals will be selected as controls. The choice of the first control is prioritized by flu-like symptoms and defined as the “symptomatic group,” including suspected or confirmed cases. Those without symptoms will comprise the “asymptomatic group;” both household and/or contact individuals can be selected, preferably paired for age and sex.

The household and/or workplace contacts were chosen to characterize the control group because of their high epidemiological value during community viral transmissions worldwide, instead of including nonusers of antimalarials with rheumatic diseases. Moreover, lupus patients without antimalarial treatment are quite uncommon, except in those with previous toxicity (maculopathy, allergy, long-term remission, etc).

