## Results

This study is in the data collection phase. Study recruitment opened in March 2020. In an 8-week period (from March 29 to May 17), a total of 10,443 individuals enrolled at baseline (including 5166 patients with rheumatic diseases) from 23 tertiary rheumatology centers in 97 Brazilian cities. Data analysis is scheduled to start after all relevant data have been collected.

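### The 20% rate behind the sample size reads as a share of infected people, while the primary aim is incidence among all enrolled; with no attack rate or target effect stated, the 80% power is unsupported

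*Protocol article*

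**What the plan says.** The Sample Size section begins "Considering a moderate-to-severe COVID-19 rate as the dependent variable", and describes this as "a rate which the current literature estimates to be 20" per cent. It adds "the proportion of 1 case for every 2 controls" and concludes that "the sample calculation was approximately 3000 antimalarial users and 6000 nonusers", "with an error α=5% and β=20" per cent. It gives no attack rate, no rate for the second group, no relative risk or difference, and no sidedness.

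Four other places bear on how the 20% should be read:

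- **Objectives:** the primary aim concerns "reducing the incidence of moderate-to-severe forms of COVID-19 in patients with rheumatic diseases", compared with household members who do not take antimalarials.
- **Data Collection:** moderate-to-severe is defined as a class of COVID-19 cases, namely those that are hospitalized, ventilated or fatal.
- **Inclusion Criteria and Control Group:** infection is not required for entry, and controls without symptoms are allowed.
- **Outcomes:** SARS-CoV-2 infection is itself listed as a primary outcome.

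The Results section reports "a total of 10,443 individuals enrolled at baseline (including 5166 patients with rheumatic diseases").

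**The concern.** A severity share among infected people and a cumulative incidence among everyone enrolled have different denominators. They are linked by the attack rate: incidence = attack rate × severe share. The two are equal only if everybody is infected. A cohort incidence of 20% would mean that one enrolled adult in five is hospitalized, ventilated or dead of COVID-19 within 24 weeks.

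If the 20% went into the calculation as the incidence, far fewer events should be expected than the calculation supposes. The practical risk is in reading the result. Under an unqualified 80% power, a null primary comparison could be taken to show no protection, when a modest benefit would probably have been missed.

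**Working it through.** **Inputs from the article.** α=5% and β=20%; outcome rate 20%; ratio 1:2; planned 3000 users and 6000 nonusers; achieved 5166 patients and 10,443 − 5166 = 5277 others.

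**Assumptions.** The test is two-sided, because sidedness is not stated. The attack rate *a* is not in the article, so a range of 5% to 50% is used. The comparison is unadjusted, with no dropout and no household clustering.

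**Formula.** For user rate p₁, nonuser rate p₀ and pooled rate p̄:

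power = Φ[(|p₀ − p₁| − 1.96 × SE₀) / SE₁], where SE₀ = √[p̄(1 − p̄)(1/n₁ + 1/n₀)] and SE₁ = √[p₁(1 − p₁)/n₁ + p₀(1 − p₀)/n₀].

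**Step 1: the plan's own figure.** With no effect stated, 3000/6000 cannot be derived forward. Solving backward with p₀ = 0.20 and 80% power gives p₁ = 0.1755, a difference of 2.45 points and a relative risk of 0.1755/0.20 = 0.877. Check: SE₀ = 0.00880 and SE₁ = 0.00865, so (0.02454 − 0.01726)/0.00865 = 0.84 and Φ(0.84) = 0.80. So the planned size fits a 20% rate over all enrolled with an unstated relative reduction of about 12%.

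**Step 2: put the attack rate in.** Let p₀ = 0.20 × *a* and keep the relative risk at 0.877. Example at *a* = 10%: p₀ = 0.0200, p₁ = 0.01755, SE₀ = 0.00307, SE₁ = 0.00300. Then (0.00245 − 0.00601)/0.00300 = −1.19, and power is 0.12.

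| Assumed attack rate | Nonuser incidence | Power at RR 0.877, planned 3000/6000 | Power at RR 0.877, achieved 5166/5277 | RR detectable at 80% power, planned | RR detectable at 80% power, achieved |
|---|---|---|---|---|---|
| 100% | 20% | 80% | 89% | 0.88 | 0.89 |
| 50% | 10% | 46% | 57% | 0.82 | 0.84 |
| 20% | 4% | 20% | 26% | 0.71 | 0.75 |
| 10% | 2% | 12% | 15% | 0.60 | 0.65 |
| 5% | 1% | 8% | 9% | 0.46 | 0.52 |

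**Step 3: does 3000/6000 fit anything else?** Yes. With 2.0% versus 1.2% (relative risk 0.60, as at a 10% attack rate), the same method needs 2986 users and 5972 nonusers. That is at least as close to the stated size as 20% versus 17.5%, which needs 2889 and 5778.

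**The case against.** The strongest reply is that the low power figures rest on a relative risk of 0.877 which the article never states. It was obtained by first supposing that 20% is the cohort incidence, so low power for that effect cannot prove that the supposition is true. Step 3 supports this: 3000/6000 also fits a calculation that already contains an attack rate. This stands. A reader might infer that the planned numbers prove the 20% was applied to everyone, that the 80% power does not exist, or that the cohort needed to be many times larger. The article supports none of these. With no target effect stated, its 80% can be neither reproduced nor refuted.

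It can also be said that the denominator of the 20% is never given and the cited sources are not at hand. That is correct, so the infected-only reading is an inference. It is a strong one. The article defines moderate-to-severe as a class of cases. Of the references cited for the 20%, the Introduction uses some for the clinical course of infected people and others for poor outcomes. Prioritizing symptomatic first controls could raise the control rate, but would not plausibly make a fifth of all controls severe.

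A third reply is that an article condenses, and the full protocol may hold the missing inputs. Their absence alone would not be a finding. The finding is that the one rate offered in support of β=20% does not, as it reads, match the outcome in the aim.

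Finally, the Control Group section plans that "For each case, two household and/or professional contact individuals will be selected as controls", and enrolment came out at 5166:5277, or 1:1.02. A reader might count this as a further error. It is not an error in the plan, and power at any given effect is higher with the achieved numbers. It matters only as an input to the restated figure.

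**Conclusion.** The concern holds in a limited form. The 20% reads as conditional on infection, the aim is incidence among all enrolled, and no attack rate or target effect connects the two. The statement of 80% power is therefore unsupported.

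If the 20% was used directly as the cohort incidence, the power for the relative risk of about 0.88 that this implies would be about 8%, 12%, 20% and 46% at assumed attack rates of 5%, 10%, 20% and 50%. These figures are conditional on that use and on attack rates the article does not give. They do not show that the study lacks power for every effect. At 2% incidence, a relative risk of 0.60 has about 80% power as planned and 90% as enrolled; a relative risk of 0.50 has 96% and 99%.

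What follows is a limit on interpretation: over plausible attack rates the cohort can detect large reductions, but a null result would not exclude a modest benefit.

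**What to change.** Rewrite the Sample Size paragraph, before outcome data are analysed, to do the following:

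- State the denominator of the 20%. If it is infected people, give expected 24-week incidence among all enrolled as attack rate × 20%, with the attack rate or a range.
- State the target effect and whether the test is two-sided.
- Replace the unqualified β=20% statement with the smallest relative risk detectable at 80% power for the achieved 5166 and 5277. Under the assumptions above this is about 0.52, 0.65 and 0.75 at attack rates of 5%, 10% and 20%.
- Add that a null result is not to be read as excluding effects weaker than these.

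The cost is one paragraph and no extra enrolment. The downside is that the stated sensitivity becomes less favourable.
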